### Data Collection and Procedures

Demographic, clinical data, and disease activity will be assessed through clinical examination and administration of an interview questionnaire. The demographic characteristics include gender, age, marital status (married/common law, single/widowed/ divorced), highest level of education (compulsory schooling, secondary school graduation, higher education), and type of occupation.

Disease-specific clinical characteristics include disease duration (months) and current medication use for each of the following categories: analgesics/nonsteroidal anti-inflammatory drugs, disease-modifying antirheumatic drugs, biologic agents (biologicals), and drugs for other medical conditions.

Pain will be assessed via a visual analog scale (VAS), a unidimensional measure of pain intensity that has been widely used in diverse adult populations, including those with rheumatic diseases. The VAS consists of a 10 cm line anchored by verbal descriptors (1=no pain at all, 10=maximum pain) [34]. The patient will be asked to place a line perpendicular to the VAS line to indicate his or her current pain intensity.

Overall disease activity will be measured with the Clinical Disease Activity Index (CDAI). The CDAI is validated and widely used [35], with the scoring done as per the following formula: CDAI = SJC-28 + TJC-28 + PGA + EGA, where SJC-28 is the Swollen 28-Joint Count (shoulders, elbows, wrists, metacarpophalangeal joints, proximal interphalangeal joints including thumb interphalangeal joint, knees), TJC-28 is the Tender 28-Joint Count, PGA is the Patient Global Assessment (patient’s self-assessment of the overall RA disease activity on a scale of 1 to 10, where 10 is the maximal activity), and EGA is the Evaluator’s Global Assessment (evaluator’s assessment of the overall RA disease activity). As proposed by the American College of Rheumatology 2008, the CDAI score will be interpreted as follows: remission = CDAI ≤ 2.8, low disease activity = CDAI > 2.8 and ≤ 10, moderate disease activity = CDAI > 10 and ≤ 22, and high disease activity = CDAI > 22.

Laboratory assessments include CRP (mg/dL), IL-6 (pg/mL), and TNF-α (ng/mL). For the detection of IL-6 and TNF-α, high-sensitivity enzyme-linked immunosorbent assay will be used, assayed in duplicates. The CRP will be measured with the patients’ routine laboratory assessments. Blood samples will be analyzed at the Institute for Laboratory Medicine of the SMZ-Süd, Vienna, Austria.

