### Aims and Objectives

The primary objective is to assess work ability in patients with seropositive RA in the working age and the association of work ability with disease activity (high, medium, low, or remission). The secondary objectives are to assess the association of muscle strength, lower extremity function, functional ability, and frailty with work ability in RA and determine the association of disease activity with selected physiological needs (sleep quality, sexual functioning) in RA.

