### Statistical Analysis

All statistical computations will be performed with SPSS version 22.0.2 (IBM Corp). The primary hypothesis of the study, “A difference in work ability and muscle strength exists in patients with high versus low disease activity,” will be tested with a Pearson chi-square test. For the descriptive statistics, mean values will be calculated for continuous variables, and categorical variables will be presented in percentages. Continuous parameters will be checked for normal distribution (Kolmogorov-Smirnov test, Levene test, histogram, and Q-Q plot check), and an unpaired Student *t* test will be performed, as appropriate. Otherwise, the Mann-Whitney U test will be used to identify differences between patients with high versus low disease activity. For categorical parameters, a Pearson chi-square test or Fisher exact test will be used if the cell count is <5. Binary logistic regression will be used to evaluate the impact of frailty, functional ability, and muscle strength on work ability. For metric data, Pearson correlation or Spearman rank correlation (given outliers or nonlinear but monotone associations) will be used to evaluate associations of interest. A *P* value of <.05 will be considered statistically significant for all tests.

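### The patient global score is stated to start at 1 and the evaluator's scale is not given, so CDAI cannot fall below 1 (or 2) and the remission band is narrowed

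*Protocol article*

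**What the plan says.** All of the scoring text is in Data Collection and Procedures of the protocol article.

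- The index is an unweighted sum: "CDAI = SJC-28 + TJC-28 + PGA + EGA".
- PGA is the patient's "self-assessment of the overall RA disease activity on a scale of 1 to 10, where 10 is the maximal activity".
- EGA is defined without a range: "EGA is the Evaluator’s Global Assessment (evaluator’s assessment of the overall RA disease activity".
- The lower categories are "remission = CDAI ≤ 2.8, low disease activity = CDAI > 2.8 and ≤ 10", and the upper ones are "moderate disease activity = CDAI > 10 and ≤ 22, and high disease activity = CDAI > 22".
- The pain scale, which is not part of CDAI, is described in the same section as a "10 cm line anchored by verbal descriptors (1=no pain at all, 10=maximum pain".

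Aims and Objectives names remission as one of four disease activity levels in the primary objective. The hypothesis in Statistical Analysis uses two levels: "A difference in work ability and muscle strength exists in patients with high versus low disease activity".

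**The concern.** The two joint counts can be zero, but a global score that starts at 1 cannot. A patient with no swollen or tender joints who reports no disease activity therefore does not score 0. The lowest cut-off is only 2.8, so a floor of even one point uses up a sizeable part of the remission band.

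CDAI category is the exposure in the primary objective. If the published cut-offs presuppose globals that start at 0, the stated scoring raises every patient's CDAI except where the offset globals are at their maximum. Patients close below a boundary are then placed one level too high. The pain scale suggests that the starting value was not handled carefully: a mark on a 10 cm line is measured from 0, yet the lower anchor is labelled 1.

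**Working it through.** **Inputs.** The CDAI formula, the PGA range of 1 to 10 and the cut-offs 2.8, 10 and 22 come from Data Collection and Procedures. The EGA minimum is not stated, so both 0 and 1 are tried. A 0-10 reference scale for the globals is an assumption, because the article gives none. The article states no CDAI minimum, so there is no figure of its own to reproduce.

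**Step 1: floor and room for remission.** Floor = 0 + 0 + min(PGA) + min(EGA). Room = 2.8 − floor.

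**Step 2: whole-number scores that give remission.** Remission needs a sum of at most 2. After subtracting the floor, count the ways in which four non-negative whole numbers sum to at most m = 2 − floor. That count is C(m+4, 4).

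| Scales | Floor | Room below 2.8 | Combinations in remission |
|---|---|---|---|
| Both globals from 0 (assumed reference) | 0 | 2.8 | C(6,4) = 15 |
| PGA from 1, EGA from 0 | 1 | 1.8 | C(5,4) = 5 |
| Both globals from 1 | 2 | 0.8 | C(4,4) = 1 |

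These are counts of score patterns, not of patients.

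**Step 3: shift against a 0-10 scale.** Map a 0-10 score x linearly on to 1-10: x′ = 1 + 0.9x. Each offset global then adds 1 − 0.1x.

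- PGA only: shift = 1 − 0.1·PGA, at most 1.
- Both: shift = 2 − 0.1·(PGA + EGA), at most 2.

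**Step 4: effect at each cut-off.**

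- *At 2.8.* No joints, PGA 1.4, EGA 1.4: CDAI 2.8, remission. PGA offset: 2.8 + 0.86 = 3.66, low. Both offset: 2.8 + 1.72 = 4.52, low.
- *At 10.* Four joints, PGA 3, EGA 3: CDAI 10.0, low. PGA offset: 4 + 3.7 + 3 = 10.7, moderate. Both offset: 4 + 3.7 + 3.7 = 11.4, moderate.
- *At 22.* With PGA 7 and EGA 7 the shift is 0.3 (PGA only) or 0.6 (both). Only patients with a CDAI above 21.7 or 21.4, and up to 22, would cross.

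The examples at 2.8 and 10 sit exactly on the cut, where any positive offset moves the patient. The shift gives the width of the affected zone. With globals of 3 each, patients above 9.3 (22 is not involved; 10 − 0.7) or above 8.6 (10 − 1.4), and up to 10, change from low to moderate.

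**The case against.** The strongest reply has four parts.

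1. **Only PGA has a stated range.** On the text alone the floor is 1.0, which leaves 1.8 points for remission. This stands. A reader might infer that remission is almost unreachable, or that a single tender joint rules it out. Neither follows. One tender joint with PGA 1 and EGA 0 gives 2, which is remission. Even with both globals starting at 1, a patient with no affected joints and minimum globals scores 2.0 and is in remission.

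2. **The upward shift needs a reference scale that the article does not contain.** This also stands. The floor and the narrower band follow from the text, whereas the reclassification depends on the 0-10 assumption and on the linear map.

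3. **Harm to the primary contrast is not shown.** A reader might infer that the 70% low-activity share in Sample Size, or the high-versus-low comparison, is distorted. No data in the article allow that to be quantified. High activity begins above 22, where the shift is smallest, and a move from remission to low leaves the high group unchanged. The cut at 10 would matter for the comparison only if the other 30% of participants, moderate included, form the second group. The article does not say so.

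4. **It may be loose wording.** The pain-scale label makes this plausible, and an article may leave the EGA scale to the full protocol. But the PGA range is a positive statement about a component of the exposure variable, so it has to be either confirmed or corrected.

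**Conclusion.** The point holds in a limited form. From the text alone, CDAI has a minimum of 1 and not 0, and the remission band is 1.8 points wide instead of 2.8. If EGA also starts at 1, the figures are 2 and 0.8.

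If the cut-offs also assume globals that start at 0, CDAI is overstated by up to 1 point (2 if both are offset). The overstatement shrinks as the globals rise. It can move patients just below 2.8 or 10 up one category, and has little effect near 22. How many patients this involves cannot be determined from the article. What is affected is chiefly the remission level named in the primary objective, together with the boundary between low and moderate.

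**What to change.** Check the case report form for the range on which PGA and EGA were recorded, and check the source of the cut-offs for the range that they assume.

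- **Recorded 0-10:** correct the PGA range in Data Collection and Procedures, state the EGA scale and correct the lower anchor of the pain scale. The analysis does not change.
- **Recorded 1-10, with cut-offs that assume 0-10:** derive CDAI with each affected global rescaled by (x − 1) × 10/9, which takes 1 to 0, 3.7 to 3 and 10 to 10. Report the category counts and the primary comparison both rescaled and as recorded. The rescaled score should not displace the recorded one until the scale behind the cut-offs is confirmed.
- **Recorded 1-10, with cut-offs set for that range:** say so and state the EGA scale. No rescaling is needed.

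The cost is a wording correction or a line of derivation code, plus a small amount of extra reporting. No new data are needed, and the Results section says that the data are still being evaluated. The downside is that linear rescaling is itself an assumption about how respondents used the scale, which is why both versions should be shown.

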### Primary Outcome

The primary outcome is self-reported work ability measured by the Work Ability Index (WAI), the most commonly used instrument to assess work ability, with an adequate test-retest reliability [36]. The WAI is a questionnaire consisting of 7 subscales: (1) current work ability compared with the lifetime best, (2) work ability in relation to the demands of the job, (3) number of current diseases diagnosed by a physician, (4) estimated work impairment because of disease, (5) sick leave during the past 12 months, (6) own prognosis of work ability 2 years from now, and (7) mental resources. The cumulative index of WAI ranges from 7 to 49 points, divided into the following 4 categories: poor (7-27 points), moderate (28-36 points), good (37-43 points), and excellent work ability (44-49 points) [37-39].

The methodological problem with using the WAI in unemployed patients is that most points of the self-evaluation reference to the current work setting. Thus, for unemployed and early retired patients, only 1 dimension of WAI, the Work Ability Score (WAS), will be assessed. The WAS comprises only the first WAI question: work ability compared with the lifetime best.

Justification on the use of WAS as 1 single question is based on previous studies that showed a high correlation between WAI and WAS [40,41]. As proposed by Gould et al [42], the classification of WAS will be conducted according to WAI as follows: poor (0-5 points), moderate (6-7 points), good (8-9 points), and excellent work ability (10 points).

### Secondary Outcomes

#### Muscular Strength Measurement

Muscle strength measurement will be performed by a trained sport scientist at the Institute of Physical Medicine situated adjacent to the rheumatologic clinic.

##### Musculus Quadriceps Femoris Maximum Voluntary Contraction Strength

Quadriceps muscle strength will be measured with an isokinetic dynamometer. The patients will sit straight with 90° flexion in the hips and with fixed hip and thigh support and arms crossed. The ankles will be fixed in a flexed position to the dynamometer, and a measuring box (Chatillon, Ametek Inc) is connected to the ankle via a length-adjustable rope. The patient will be instructed to perform 1 maximal voluntary contraction of the quadriceps muscle. Strength will be assessed 3 times for both legs with a 2-minute break between measurements. The mean value of both legs will be used in the statistical analysis.

##### Maximal Voluntary Isometric Hand Grip Strength

The maximum grip strength will be measured with a portable Jamar hydraulic hand dynamometer (Patterson Medical). The patients will be examined in a standard position, in which they sit upright with their upper arm adducted and the elbow flexed at 90°. The dynamometer will be used according to the instructions in the operating manual. The dynamometer will be placed in a patient’s hand, and after the instruction is given, 3 maximum voluntary grip strength contractions will be performed with each hand. Measurements will be done in an alternating order with a 2-minute break between measurements. The mean value of each hand will be recorded for analysis.

#### Functional Disability

The Health Assessment Questionnaire Disability Index (HAQ-DI) will be used to assess the extent of patients´ self-reported functional disability. The HAQ-DI has been used to measure functional status in RA in multiple settings and languages since 1980, and it has shown good reliability and validity [43]. It examines patients’ usual abilities in using their regular equipment during the past week. The scoring of the HAQ-DI is patterned after the functional classes of the American Rheumatism Association/American College of Rheumatology. A total of 20 questions are included in the following 8 categories of functioning: dressing, rising, eating, walking, hygiene, reach, grip, and usual activities.

Self-reported difficulties to perform these activities are scored on a scale from 0 to 3, representing normal (no difficulty) (0), some difficulty (1), much difficulty (2), and unable to do (3). For any component question, the highest score determines the score for that respective domain. The overall disability index is a value between 0 (no functional disability) and 3 (severe functional disability), representing the average score across the domains [44].

#### Survey of Health, Ageing, and Retirement in Europe Frailty Instrument

Frailty will be assessed with the Survey of Health, Ageing, and Retirement in Europe Frailty Instrument (SHARE-FI). This instrument was developed on the basis of the results of the Survey of Health, Ageing and Retirement in Europe and serves as a rapid measurement tool with good predictive validity. The assessment comprises 5 variables: grip strength measurement and 4 questions related to weakness, exhaustion, slowness, and activity level. With the use of the 5 variables, DFactor scores will be calculated with the gender-specific SHARE-FI formula. For each participant, the frailty score will be computed, and the participants will then be categorized as nonfrail, prefrail, or frail [45].

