### Sample Size

The sample size was calculated to determine the difference in work ability between patients with high versus low disease activity. We estimate the percentage of patients with good work ability to be 40% in patients with high disease activity and 80% in patients with low disease activity. Furthermore, we estimate that 70% of the included participants will have a low disease activity. With an alpha risk of .05 and a beta risk of .2 accepted in a 2-sided test, 71 patients need to be included (results were obtained with nQuery Advisor 7.0, Statcon). With a 30% rate of loss assumed (because of noncompliance during physical tests, lack of understanding, or refusal to participate), a total of 100 included patients will be required.

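### The secondary analysis collapses four ordered work-ability categories to a binary outcome and leaves room for frailty and grip strength, which overlap by construction, to share one model

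*Protocol article*

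**What the plan says.** All references are to the protocol article.

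- **Statistical Analysis** names the method for the determinants: "Binary logistic regression will be used to evaluate the impact of frailty, functional ability, and muscle strength on work ability". It does not say whether the determinants share one model, how each is coded, or where work ability is cut.
- **Primary Outcome** gives a WAI of 7 to 49 points for employed patients and a single-item WAS of 0 to 10 for unemployed and early retired patients. Both are classified as poor, moderate, good or excellent.
- **Sample Size** contains the only binary use of work ability: "We estimate the percentage of patients with good work ability to be 40% in patients with high disease activity and 80% in patients" with low activity. It adds that "we estimate that 70% of the included participants will have a low disease activity".
- **Survey of Health, Ageing, and Retirement in Europe Frailty Instrument**: "The assessment comprises 5 variables: grip strength measurement and 4 questions related to weakness, exhaustion, slowness, and activity level". A frailty score is computed, and patients are then put into three classes.
- **Maximal Voluntary Isometric Hand Grip Strength**: "The mean value of each hand will be recorded for analysis". This section stands under Muscular Strength Measurement, and the abstract's Methods also count grip and quadriceps strength together as muscle strength.

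**The concern.** Two features of the stated analysis weaken the answer to the secondary objective, which asks how strength, function and frailty relate to work ability.

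First, the outcome is made binary although four ordered categories exist for every patient. A binary model treats poor and moderate alike, and good and excellent alike. That costs precision in a study of about 100 patients sized only for the primary two-group comparison.

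Second, measured grip strength is both a muscle-strength determinant and an ingredient of the frailty score. In a model holding both, the frailty coefficient would describe frailty at fixed grip, although grip helps to define frailty, and the grip coefficient would be read net of a score that contains it. The article hopes its findings will encourage interventions on muscle strength, so the strength coefficient should have a clear meaning.

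**Working it through.** **Inputs (Sample Size section).** Good work ability 40% with high and 80% with low disease activity; 70% of patients with low activity, hence 30% high; 71 evaluable and 100 included patients. I assume that good means good or excellent, since the cut for the logistic model is not stated.

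**The plan's own figure.** The article gives no event count for the logistic model, so there is nothing to reproduce for it. I take 71 and 100 as given. The usual two-proportion formulas with the stated inputs at 80% power give about 50 to 54 patients uncorrected and 62 to 64 with continuity correction; only 90% power comes close (70). That is a separate matter and does not affect the outcome split below.

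**Step 1, outcome split.**
- Good: 0.30 × 0.40 + 0.70 × 0.80 = 0.12 + 0.56 = 0.68.
- Not good: 1 − 0.68 = 0.32.
- Smaller class: 0.32 × 71 = 22.7; 0.32 × 100 = 32.
- If the share with high activity is varied from 10% to 50%, the smaller class is 17 to 28 of 71, or 24 to 40 of 100.

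**Step 2, information kept by the binary cut.** Assume a normal latent work-ability score and small effects. Relative information is φ(z)² / [p(1 − p)] with p = 0.32. Here z = −0.468 and φ(z) = 0.3576, so 0.1279 / 0.2176 = 0.588. About 59% is kept and 41% lost, relative to the undivided latent score.

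**Step 3, what four categories would keep.** The sum over categories of (difference of φ at the two bounds)² / category share gives the corresponding figure. The article does not give the category shares, so I show two assumed splits that respect 32/68 (poor/moderate/good/excellent):
- 16/16/34/34: 0.370 + 0.082 + 0.000 + 0.395 = 0.847. The binary model keeps 0.588 / 0.847 = 69% of what the ordinal model uses.
- 4/28/64/4: 0.186 + 0.263 + 0.115 + 0.186 = 0.750. The binary model keeps 0.588 / 0.750 = 78%.

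Against the realistic alternative the loss is therefore roughly 22% to 31% in these two cases, less than the 41% of Step 2.

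**Step 4, events per term if one joint model were fitted.**

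| Model | Terms | 71 patients | 100 patients |
|---|---|---|---|
| One determinant | 1 | 22.7 | 32.0 |
| One determinant plus CDAI | 2 | 11.4 | 16.0 |
| Three constructs, one term each | 3 | 7.6 | 10.7 |
| Frailty score, HAQ-DI, quadriceps, grip | 4 | 5.7 | 8.0 |
| Same, frailty in three classes | 5 | 4.5 | 6.4 |

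**Step 5, overlap of frailty and grip.** No correlation is given. For assumed r = 0.5, 0.7 and 0.9, the variance inflation 1 / (1 − r²) is 1.3, 2.0 and 5.3. Variance inflation may thus be modest; the difficulty of interpreting the two coefficients remains whatever r is.

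**The case against.** The strongest reply is that the article does not state a joint model. Its sentence on logistic regression fits separate models equally well. With one determinant per model there are 22.7 to 32 events for one term, and grip never meets SHARE-FI. This stands. A reader might infer that the plan enters frailty and grip together and has too few events for its predictors. The text does not support that: no predictor list is fixed, and counts of six or more terms need the costliest coding throughout (three frailty classes, each hand separately), then SPPB, which the logistic sentence does not name, or confounders the article does not plan. Even the three named constructs at one term each are borderline at worst. Quadriceps strength is not part of SHARE-FI, so the strength question would not become unanswerable.

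It can also be said that coding and cut-point belong to an analysis plan not shown, and that the article plans Pearson or Spearman correlations for metric data. The first is fair for details, but the choice of a binary model is stated here. The second softens the loss without removing it: the correlations are unadjusted, and WAI points and WAS points are not on one scale.

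One might go further and replace the outcome by linear regression on WAS for everyone. That would drop six of the seven WAI subscales for employed patients and displace the declared primary instrument. The four shared categories avoid this.

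**Conclusion.** The point holds as a cheap improvement, not as an error that invalidates the analysis. The unconditional part is the binary outcome: it discards information whether determinants enter singly or jointly. The size is about 41% against a continuous latent score and roughly 22% to 31% against the four categories. These figures rest on a normal latent score, on the article's planning rates and, for the second range, on assumed category shares.

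The conditional part is the overlap. The wording allows frailty and grip to share a model. If they do, their coefficients overlap by construction, and about 23 to 32 events give about 4.5 to 8 per term for 4 to 5 terms. Any threshold for what is enough is a convention from outside the article. Claims that the odds ratios will be biased, or that separation will occur, go beyond what the document shows. The analysis is secondary, in a study described as hypothesis-generating.

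**What to change.** 1. Make a proportional-odds model on the four work-ability categories the main determinant analysis. Keep binary logistic regression as supportive, with the cut stated.
2. Fit each determinant in its own small model with CDAI as a covariate. The introduction links higher disease activity to impaired strength, and the Sample Size section assumes it moves good work ability from 80% to 40%, so by the article's own account it can confound the strength association.
3. Do not enter SHARE-FI and grip strength in the same model.
4. Use one grip value per patient, averaged over both hands.

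Cost: a few sentences in the plan and little extra analysis; no new data. The proportional-odds assumption must be checked, and there will be no single mutually adjusted model of all determinants. Enrolment is complete and data are being evaluated, so the change should be documented as made before analysis or, if that is no longer possible, reported as a sensitivity analysis.
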